## Abstract

Children with congenital Zika syndrome (CZS) present severe motor disability and can benefit from early powered mobility. The Go Zika Go project uses modified ride-on toy cars, which may advance the body functions, activities, and participation of children. This paper describes the study protocol aiming to assess the feasibility of a modified ride-on car intervention for children with CZS in Brazil. A mixed-methods design with a multiple 1-week baseline, 3-month intervention, and 1-month follow-up will be implemented. Modified ride-on car training sessions will be conducted three times a week at the participants’ home or in the clinic. The primary outcome will be a narrative description of study feasibility (photovoice method, focus groups, parent feasibility questionnaire and assessment of learning powered mobility). Secondary outcomes will be switch activation, driving sessions journal, social-cognitive interactions, mobility (pediatric evaluation of disability inventory computer adaptive test), goal attainment scaling (GAS), and participation (young children’s participation and environment measure). Go Zika Go is expected to be viable and to improve function, activity, and participation of children with CZS, providing a low-cost, evidence-based rehabilitation option that will be relevant to early child development in a global perspective.

## 1. Introduction

Congenital Zika syndrome (CZS) became a global concern after the Zika virus outbreak in 2015, which mainly affected Brazil [1]. The situation is more serious in the Northeast region, which concentrates the majority of cases, and is marked by strong social problems, scarcity of investments in the training of human resources and in the provision of health services [2]. Children with CZS have severe motor disability, the majority of them compatible with Gross Motor Function Classification System (GMFCS) classification V (i.e., no prognosis for independent mobility) [3]. Only one study evaluated the profile of functioning of children with CZS in Brazil, demonstrating that activity and participation were highly impacted, and that societal attitude was the main barrier to participation [4]. To date, only one preliminary study has been published on the rehabilitation of children with CZS between 3 and 9 months of age. The results indicated that the intervention program based on the principles of Goals-Activity-Motor Enrichment (GAME) improved mothers’ assessment of their babies’ performance, and satisfaction with the performance of functional priorities and the perception of an enriched home environment [5]. 

As CZS is a completely new condition, rehabilitation approaches more commonly used are based on recommendations for cerebral palsy (CP). Even for CP, evidence-based interventions are more easily available for children with mild to moderate motor impairment, and interventions are limited for children with severe motor impairment [2,6]. Young children with typical development exhibit gains in cognitive development, communication, and social skills after starting independent walking [7,8,9]. Young children with motor disabilities are often not able to take part in self-initiated mobility, and are more likely to experience cognitive and developmental delays, as well as less social interactions with caregivers and peers [10,11].

For young children with disabilities, early powered mobility may advance the body function, activity, and participation, in contrast to other interventions within pediatric rehabilitation which are often focused exclusively on one physical skill (body structure domain) in isolation of other therapeutic goals within a stagnant clinical environment (ex. treadmill training). Research indicates positive results of powered mobility interventions for young children with functional impairments [11,12] since battery-operated ride-on cars are easily modified and are considered as an option of increasing interest for motorized mobility for children with disabilities.

Globally, there are very few commercially available motorized wheelchairs for young children with disabilities and existing options are extremely expensive (>USD 17,000 for a base model) [13]. Environmental inaccessibility and device characteristics inhibits motorized wheelchair use [12,13,14,15].

The low cost of modified cars (<USD 400) can minimize some of the barriers previously reported, such as an inaccessible physical environment, financial impact, and peculiarities of motorized wheelchairs readily available commercially. The modifications are fundamental and include the use of large and easy-to-press actuators generally positioned on the steering wheel; in addition to the requirements to provide stability in the seat using common materials, such as polyvinyl chloride (PVC) pipe, swimming kickboards, and Velcro. 

Several studies have showed the results of a powered mobility intervention with modified ride-on car on the behavior and development of young children with disabilities, including CP. Although none of the children in these studies were formally referred to use powered mobility devices due to their young age or diagnosis, all demonstrated the ability to independently press the activation switch, enjoyed driving sessions, and some experienced increased self-care mobility [16], social skills [16,17], as well as increased peer interaction on the playground [18], and during an inclusive playgroup [19]. The limitations of previous work includes a heavy reliance on low-evidence level research designs (i.e., case reports and case series); the inclusion of participants with varying disabilities in the same sample; and the reporting of a wide variety and often very low adherence rates to recommended use guidelines. These limitations have hindered the interpretation and generalization of study results and will be addressed in the current protocol. 

Although participation-based interventions are a promising strategy not only to improve participation but also body functions [20], there are no evidenced-based practices to guide clinical recommendations of early powered mobility device use, including modified ride-on cars, for young children with disabilities, including CZS. The current protocol will address this gap in knowledge and will have a direct and immediate impact on clinical practice. From a global health standpoint, the results may provide an evidence-based rehabilitation option that will be relevant to early child development in low resource contexts. The objective of this study is to determine the feasibility of a powered mobility intervention for young children with CZS with severe motor impairment including acceptability and effectiveness. The specific aims are:To evaluate the acceptability of a modified ride-on car intervention for young children with CZS and their families.To determine the effect of a modified ride-on car intervention on the (a) mobility and social function, and (b) participation of young children with CZS and their families.To understand the barriers and facilitators of a modified ride-on car intervention for young children with CZS and their families.

## 2. Materials and Methods

### 2.1. Design

This is a feasibility trial of a mixed-methods case series, prospectively registered, with 3-month intervention and 1-month follow-up. The follow-up will aim to assess preliminary learning retention and implications of modified ride-on car training sessions [16]. This prospective study will provide important information about the feasibility, assistive effectiveness, and rehabilitative effectiveness of the first intervention focusing on powered mobility for children with CZS in Brazil. The procedures and timeline of the study are included in Figure 1 and Table 1.

### 2.2. Participants

Inclusion criteria: (a) Diagnosis of CZS, (b) GMFCS [21], level IV or V, (c) aged between 1.5 and 5 years, (d) no previous experience with powered mobility. 

Exclusion criteria include the presence of uncontrolled seizures and musculoskeletal deformities that prevent adaptation of the seating support in the device. 

### 2.3. Sample Size Estimation

In this feasibility study, we will recruit 10 children with CZS. This small sample will provide data on the feasibility of the protocol, thus helping determine the sample size for a larger randomized trial using powered mobility in children with CZS. Given the lack of previous studies measuring the outcomes of interest for this study, the sample size was estimated according to recommendations of the minimum sample for pilot studies [22].

### 2.4. Settings and Locations Where the Data Will Be Collected

The scenario of CZS in Brazil is 3523 confirmed cases, with the Northeast region being the most affected, with 1907 cases. Rio Grande do Norte, where this study will occur, is one of the 9 states in the Northeast region and has 126 confirmed cases of CZS. In the national gross income ranks, it occupies the 17th position among the 34 Brazilian states. In 2010, the Human Development Index of Rio Grande do Norte was 0.684 and ranked 16th among the 27 federative units in the country. 

Recruitment of participants will take place through early intervention services, pediatric clinics that provide physical and occupational services, and community-based programs that serve the study populations throughout Rio Grande do Norte (RN) state in Brazil. The recruitment will take place between January and December 2021.

### 2.5. Patient and Public Involvement

Parents’ involvement in the design of the protocol: parents or caregivers of children diagnosed with CZS who received a rehabilitation service at Clínica Escola de Fisioterapia da Facisa—[name] were asked to answer a questionnaire prepared by the researchers, with 8 questions related to intervention preferences. Initially, the parents watched a video about the Go Zika Go project and then they were interviewed by the first author (EL) at the clinic or at home. The questions included aspects of the families’ interest in participating in the intervention, space available at home to use the ride-on car, ideal time for mobility training, preference for the place to perform the intervention, etc. Five parents/caregivers participated in this exploratory stage of the research. The results of this stage showed that all families were interested in participating in the intervention and stated that the training can be performed at home and/or at the clinic setting.

### 2.6. Outcomes Measures

#### 2.6.1. Primary Outcome

The primary outcome of the study will be the feasibility of the protocol, including a narrative description, recruitment and retention rates, adherence and acceptability of the protocol. A mixed methods approach will be used to assess the primary outcome.

A document analysis will determine the number of parents who received information about the study by mail, the number of potential participants contacted by telephone, how many parents met the inclusion criteria and how many provided informed consent, received, and completed the intervention. 

Qualitative data will be collected using the photovoice method and focus groups. Photovoice is a participatory action-research modality that uses photographs to express individuals’ experiences during their daily realities [23].

Photovoice aims to record and present everyday realities using photography; promote dialogue and critical reflection of reality and know the strengths and weaknesses of the target audience; and reach decision makers [24]. Photovoice will explore families’ perception of the feasibility of modified ride-on cars for children with CZS at home and in the community. In the eighth week of the intervention, the parents of children with CZS will be invited to participate in a focus group to provide information about the application of photovoice, its ethical aspects, to clarify doubts about the handling of cameras, expectations in participation and to solve personal issues that may arise. Thus, the methods will follow the Wang and Burris [25] recommendations. Disposable cameras will be offered to record the photos. Parents or caregivers who prefer not to use the camera offered by the researchers will use the cameras on their smartphones and share information by the messaging app. Guidance will be provided on how to capture quality photos, and information about the privacy of people in the scene to be photographed. Parents/caregivers will be instructed to photograph moments of the child’s routine at home and in the community. To guide the capture of the photos, parents/caregivers should follow a script of questions asked by the researchers, which include: (1) How does my child feel when using the modified ride-on car? (2) Does the modified ride-on car help my child to get around at home and in the community? (3) Does the modified ride-on car help my child to play with other children? When and where is the modified ride-on car used? Participants will be instructed to capture photos that answer study questions over the next 4 weeks (the third month of intervention). It is recommended that each participant register between 20 and 30 photos [25]. After this period, digital images or printed photographs will be delivered to the research team for the preparation of the second focus group. 

In the 12th week of the intervention, the second focus group will be held, where the photos will be displayed and shared with the researchers and other participants, so that the images can be discussed, allowing for a deep reflection from the creation of a proper reading of each moment, on the use of modified ride-on cars by children with CZS at home and in the community. Each participant will be asked to select the most significant pictures representing the experience of their children using the ride-on car. The showed method [26] will be used through its specific questions to facilitate assistance to participants in contextualizing the meaning of their photographs. In addition to the discussion on the contents of the photos, the following feasibility questions guide will be used: What is your perception of the intervention with modified ride-on cars? What helped or hindered your child’s use of the modified ride-on cars at home and in the community? Do you think the intervention was useful for your child? All focus groups will be conducted in person by two members of the research team. The sessions will be recorded in audio and video, transcribed and analyzed thematically [27,28]. 

Quantitative data will be collected from feasibility questionnaires for parents and professionals. The parents feasibility questionnaire (PFQ) [29,30] includes questions related to satisfaction with the intervention, the time of use at home and in the community, the usefulness of the ride-on car, the level of comfort related to the time of its use and the need for help from others during use. PFQ will be used at the end of week 4, 8, and 12 of the intervention, and at follow-up. The assessment of learning powered mobility (ALP) [31] will be used to measure the feasibility of the intervention. This tool is able to describe the learning process’ phase at the initial stages of using a powered mobility device. It also documents the child’s occupational performance, thus supporting the selection of learning strategies. Phases are scored from 1 (novice) to 8 (expert) to describe occupational performance while using a powered mobility device, considering five categories: understanding of tool use, level of attention, expressions and emotions, activity and movement, and interaction and communication [31,32]. In this study, the ALP will be applied at the end of weeks 4, 8, and 12 of the intervention, and at the follow-up. In addition, a sociodemographic questionnaire will be used for all participants at the baseline.

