#### 2.6.2. Secondary Outcomes

##### Switch Activation

Switch activation is defined as when the switch is pressed to activate the modified ride-on car and make it “go”, thereby moving in space from one place to another [30]. Switch activation may occur from the child in the modified ride-on car independently or with assistance (either physical or verbal cueing) from others. Assistance may be provided by a sibling or peer, or an adult such as a parent/caregiver or clinician. The duration of switch activation, who activated the switch, and the level of assistance, if any, provided to the child using the modified ride-on car will be coded. Total switch activation time (minutes and seconds) and percentage of time of each 10-min video will be coded and reported. Switch activation analyses will be carried out at the end of week 4, 8, and 12 of the intervention.

Inter- and intra-rater reliability (at least 85% agreement) will be established on 10% of the video recordings amongst one expert coder and two secondary coders. Training will include coding of video recordings, discussion of disagreements, and coding of additional videos until reliability is established. All videos will be coded in Datavyu.

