### 2.7. Intervention

Modified ride-on car training sessions will be conducted three times a week at the participants’ home or in the clinic, according to family preference. A therapist will guide the sessions at both locations. The intervention session will include the following: (1) environment setup (e.g., instructing families) (5 min); (2) natural play as a warm up activity (5 min); and (3) social training and mobility with modified ride-on cars (30 min). The focus of treatment sessions will be based on the social function goals and the expected mobility set by caregivers in the modified GAS after the pretest [36]. The 30-minute driving session will involve the participants learning cause–effect concepts by driving the modified ride-on car (i.e., pressing the switch for moving and releasing it for stopping). The dose of the intervention will be adjusted considering the opinion of the parents who participated in a previous interview and the results of a recent study, where the average time of interventions was 24 to 30 min [37]. The therapist and caregivers then will use verbal and physical cueing to encourage children to drive and explore the surrounding environment [17,38]. All sessions will be video- and audio-recorded. Figure 2 shows a modified ride-on car and a child with CZS.

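### ALP and switch activation are first measured after 12 of the 36 planned sessions, so change in driving has no measured starting point

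*Protocol article*

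**What the plan says.** Section 2.6.1 of the Protocol article gives the ALP schedule: "the ALP will be applied at the end of weeks 4, 8, and 12 of the intervention", and once more at follow-up. It gives the tool a feasibility role, in that it "will be used to measure the feasibility of the intervention", and explains what it captures: "This tool is able to describe the learning process’ phase at the initial stages of using a powered mobility device". The scale runs from 1 to 8 over five categories.

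Section 2.6.2 (Switch Activation) states: "Switch activation analyses will be carried out at the end of week 4, 8, and 12 of the intervention". Presses made with help count as activation; who pressed and how much help was given are coded as well.

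Table 1 agrees with the text. Neither measure is marked at week 0, and switch activation is not marked at week 16. PEDI-CAT, YC-PEM and GAS all have a baseline.

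Other relevant places:
- Section 2.2 admits only children who are new to powered mobility.
- Section 2.1 gives the purpose of the last visit: "The follow-up will aim to assess preliminary learning retention".
- Section 2.7 sets three sessions a week, each with 30 minutes of driving, and adds: "All sessions will be video- and audio-recorded".
- Section 2.9 assigns the Friedman test to numerical outcomes with more than two measurements.

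**The concern.** By the protocol's own account the ALP is informative when a child first meets the device. For children who have never driven, that is the first weeks of training, and this is the one stretch of the intervention without an ALP score or a coded switch value. The sessions teach the child to press to move and release to stop. Switch activation measures that skill, yet it too begins only after a month of practice.

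The study is an uncontrolled series of 10 children, so change within each child is its only quantitative evidence of learning. If the first value is taken at week 4, a good week-4 level may reflect learning in weeks 1 to 4 or ability present at entry, and the data cannot separate the two. The results are also meant to help size a larger trial (section 2.3). A change measured from week 4 would not represent change from the start of training.

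**Working it through.** The plan states no figure to reproduce here: the sample of 10 rests on a cited minimum for pilot studies. The check is of the schedule and its consequences.

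**1. Training delivered before the first measurement** (sections 2.1 and 2.7, full attendance assumed)
- Sessions: 3 × 4 = 12 of 3 × 12 = 36, or 33%.
- Driving time: 12 × 30 = 360 of 36 × 30 = 1,080 minutes.

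**2. What the tests cover**
- ALP: four measurements (weeks 4, 8, 12, 16). Friedman compares levels within that span.
- Switch activation: three measurements (weeks 4, 8, 12).
- Neither test includes change before the end of week 4. They do span the remaining 36 − 12 = 24 sessions, so the larger part of training is observed.

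**3. Share of the 12-week gain that falls before week 4.** The documents give no learning curve, so every line below is an assumption.
- Linear: 4/12 = 33%.
- Front-loaded (exponential with time constant τ weeks): share = (1 − e^(−4/τ)) / (1 − e^(−12/τ)).

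| τ (weeks) | 2 | 3 | 4 | 6 | 8 | 12 |
|---|---|---|---|---|---|---|
| share missed | 87% | 75% | 67% | 56% | 51% | 45% |

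- Slow start, for example gain proportional to time squared: (4/12)² = 1/9 = 11%.

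The share thus runs from about a tenth to well over four fifths, depending only on the curve chosen.

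**4. Can the starting value be presumed instead?**
- ALP: partly. Eligibility suggests a start near the novice end. But the five categories include attention, emotional expression and communication, in which children may differ at entry.
- Switch activation: no. Assisted presses count, so first-session time need not be near zero. Section 2.8 says most earlier work used an all-or-nothing switch while this study fits a joystick, so earlier studies do not supply a value either.

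**The case against.** - **The level at week 4 is informative in itself.** A reader might infer that a child who learned early and levelled off cannot be told from one who never learned. That is true only of the Friedman test: a child constant at ALP 6 and a child constant at ALP 1 both contribute tied ranks. The two levels are plainly different, and section 2.9 reports descriptive statistics. This objection stands. What remains is that the level does not show whether it was acquired or already there.
- **Retention is measured.** A reader might infer that the follow-up fails its purpose. It does not. Retention compares week 16 with week 12, and the ALP is taken at both; the parent questionnaire and driving journal also continue. Switch coding at week 16 would add a second observed measure and is optional.
- **No learning hypothesis is stated.** The ALP is labelled a feasibility measure, and the effect aim (mobility, social function, participation) is served by instruments that have a baseline. This is fair and limits the weight of the point. Still, the protocol's description of the ALP, the session content and the follow-up aim all concern learning.
- **The gap is recoverable.** Early video will exist whatever the schedule says. That holds for switch activation, but coding it unplanned would be a later choice. The article does not say that the ALP can be scored from video.
- **The measure itself needs settling.** Section 2.6.2 defines pressing a switch while section 2.8 fits a joystick. These passages should be reconciled before any clip is coded, at week 1 or later.

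**Conclusion.** The point holds as a design weakness. It is not a contradiction, since text and Table 1 agree. Both measures that observe driving begin after 12 of 36 planned sessions in children new to powered mobility, and the planned tests cover only change after week 4. The study cannot show from measured data how a child's week-4 level divides between learning and ability at entry. The gap is most serious for switch activation; for the ALP, eligibility offers a presumed but unmeasured start.

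The size of the loss is unknown. It is 33% of the 12-week gain under linear learning, more under early learning and less under a slow start, which is conceivable in children at GMFCS IV or V. A reader might take the front-loaded figures to mean that more than half of the gain is missed; the documents contain nothing that selects those curves. The session count assumes full attendance. Figure 1 is not shown and the abstract's one-week baseline is not elaborated; nothing visible places either measure there.

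**What to change.** 1. Code switch activation from the recording of the first driving session in week 1.
2. Score the ALP for that session, at the session itself or from the video if the tool allows it.
3. Name these values as the reference for change in section 2.9, and add both to Table 1.
4. Optionally, film the week 16 ALP assessment and code switch activation from it, so that retention also has the coded driving measure.

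Cost, assuming one 10-minute clip per child and time point:
- 10 extra ALP scores.
- Steps 1 to 3: 10 extra clips, 10 × 10 = 100 minutes of footage, on top of the 10 × 3 = 30 clips already planned.
- With step 4: 20 extra clips, 200 minutes or about 3.3 hours.

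Coding takes longer than the running time. No extra visit is needed for the first session. Training sessions end at week 12, so step 4 needs a filmed drive at week 16; the article does not say whether the follow-up already includes one.
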